**Methods:**

A parallel-group, block-randomized clinical trial will compare ePT and uPOD. Both groups will be seen initially by a podiatrist before allocation to a group that will receive physical therapy intervention consisting primarily of manual therapy, exercise, and modalities, or podiatric care consisting primarily of a stretching handout, medication, injections, and orthotics. Treatment in each group will be directed by practice guidelines and a procedural manual, yet the specific intervention for each participant will be selected by the treating provider. Between-group differences in the Foot and Ankle Ability Measure 6 months following the initial visit will be the primary outcome collected by an independent investigator. In addition, differences in the European Quality of Life – Five Dimensions, Numeric Pain Rating Scale, Global Rating of Change (GROC), health-related costs, and cost-effectiveness at 6 weeks, 6 months, and 1 year will be compared between groups. The association between successful outcomes based on GROC score and participant expectations of recovery generally, and specific to physical therapy and podiatry treatment, will also be analyzed.

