#### Primary outcome measure

The FAAM ADL subscale will be used to assess participant-reported functional outcome. The FAAM has demonstrated an intraclass correlation coefficient of 0.89 and a MCID of 8 for the ADL subscale [30].

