### Statistical analysis

Baseline group variables will be summarized using the mean and standard deviation for continuous measures and percentages for categorical measures. Independent *t*-tests (*P* <0.05, two-tailed) or the appropriate nonparametric test will be used to compare between-group differences in baseline characteristics (Table 1). Parametric test assumptions will be analyzed for all continuous variables by visual inspection of histograms, use of skewness score within double the standard error of skewness criteria, and Levene’s test for homogeneity of the variance. A repeated measures analysis of variance will be used to compare group differences in the FAAM, NPRS, EQ-5D™, and number of office visits associated with treatment at each time point. Results will be reported as the group mean, mean difference between groups, 95% confidence intervals, f-value, *P* value, power, and effect size. The χ^2^ test will be used to compare GROC scores between groups at each time point and results will be reported as the χ^2^ value, *P* value, and the frequency per category. The types of treatment based on Current Procedural Terminology and Healthcare Common Procedure Coding System codes provided per group will be reported as percentages. Analysis of covariance will be used if any group differences are observed in participant characteristics. Intention-to-treat analysis will be performed by comparing the complete case analysis to multiple imputation analysis. Multiple imputed data sets will be generated using the Multivariate Imputation by Chained Equations algorithm with SPSS 19.0 for Windows (SPSS Inc., Chicago, IL, USA). Multinomial logistic regression will be used to obtain pooled regression estimates from the data sets that will be used for analysis. Post-randomization exclusion of included participants that did not meet eligibility criteria or that did not receive intervention will be considered for exclusion of the analysis by an independent, blinded adjudication committee that will evaluate all randomized participants [57]. Any crossovers will be analyzed in the original group to which they were assigned. A separate analysis excluding crossovers will be performed.

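### Estimates from the imputed data sets are to be pooled from multinomial logistic regression, which cannot give the 6-month FAAM mean difference, and the plan does not say whether the complete-case or the imputed result decides

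*Protocol article*

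**What the plan says.** The Abstract (Methods) fixes the primary comparison: "Between-group differences in the Foot and Ankle Ability Measure 6 months following the initial visit will be the primary outcome". The section Primary outcome measure names the instrument: "The FAAM ADL subscale will be used to assess participant-reported functional outcome". The Participants section gives that subscale a maximum of 84.

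The Statistical analysis section then makes five statements that bear on this point:

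- Model: "A repeated measures analysis of variance will be used to compare group differences in the FAAM, NPRS, EQ-5D™, and number of office visits".
- Reported quantity: "Results will be reported as the group mean, mean difference between groups, 95% confidence intervals, f-value, *P* value, power, and effect size".
- Intention-to-treat: "Intention-to-treat analysis will be performed by comparing the complete case analysis to multiple imputation analysis".
- Imputation: "Multiple imputed data sets will be generated using the Multivariate Imputation by Chained Equations algorithm with SPSS 19.0 for Windows".
- Pooling: "Multinomial logistic regression will be used to obtain pooled regression estimates from the data sets that will be used for analysis".

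The same section keeps crossovers in the group to which they were assigned, and it sends GROC to a χ² test.

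**The concern.** Multinomial logistic regression is a model for an outcome with unordered categories. FAAM, NPRS and EQ-5D are scores that the same section analyses and reports as means. If the pooling sentence applies to them, and nothing in it says otherwise, the imputed-data analysis produces odds ratios where the plan promises a mean difference and a confidence interval.

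This matters most for the primary outcome. The imputed analysis is the one meant to bring back participants with missing FAAM scores, and it is the half of the comparison labelled intention-to-treat that keeps them. If it cannot be expressed in FAAM points, it cannot be set beside the complete-case mean difference, which is what the plan intends to do.

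The second issue is smaller. A comparison of two analyses is not itself an analysis. If the two disagree, the text does not say which one answers Aim 1, so that choice could be made after both results are known.

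**Working it through.** **1. Confirm that the design targets a difference in points.** The sample size paragraph under Participants gives a 9-point difference, a spread of 14.5, alpha 0.05 and 80% power.

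- Standardised effect: 9 / 14.5 = 0.62, as stated. This takes 14.5 as a standard deviation, although the article calls it a variance.
- Two-sample t-test, two-sided 0.05: 42 per group gives 80.3% power, so the stated 42 is reproduced.
- Inflation: 42 × 1.33 = 55.9, which rounds to the stated 56.

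The calculation is for a difference between two means, which agrees with the ANOVA and with the promised mean difference.

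**2. Compare what is promised with what each named model returns.**

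| Step | Named method | Returns | Gives the FAAM difference in points? |
|---|---|---|---|
| FAAM, NPRS, EQ-5D comparison | Repeated measures ANOVA | Group means and their differences | Yes |
| Pooled estimates from imputed data | Multinomial logistic regression | Log odds ratios against a reference category | No |

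**3. Try to apply the sentence to FAAM literally.** If the subscale runs in whole points from 0 to 84 (an assumption; the article gives only the maximum), there are 85 possible values. A multinomial model that treats each as a category has up to 85 − 1 = 84 arm coefficients, from 2 × 56 = 112 participants. None of them is a mean difference.

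**4. Illustrate on one simulated data set.** Assumed: 56 per group, normal scores with the ceiling ignored, control mean 70, true difference 9, SD 14.5.

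- Linear regression on arm: 8.54 points, SE 2.37. The 95% CI is 8.54 ± 1.98 × 2.37, about 3.8 to 13.2 points.
- Multinomial regression on the same scores cut into thirds: two log odds ratios, 0.46 and 1.76 (odds ratios about 1.6 and 5.8), with no estimate or standard error in points.

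The cut into thirds was made only so that the model could be fitted. It is not part of the plan. The example shows the kind of output and does not measure any loss.

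**5. Check what pooling requires.** Rubin's rules average the same quantity over the m imputed data sets: estimate = (1/m) Σ Q_k, and variance = Ū + (1 + 1/m) B, where Ū is the mean within-data-set variance and B the between-data-set variance. To obtain a pooled mean difference, each Q_k must be a mean difference. A multinomial coefficient does not supply one.

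**6. Look for a rule that decides.** The intention-to-treat sentence names two analyses. Neither it nor the rest of the section calls one of them primary or says what follows if they differ. The crossover sentence settles group membership, not the handling of missing scores.

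**The case against.** The strongest reply is that the pooling sentence does not mention FAAM, and that the ANOVA and the mean difference are fixed in the same section. Two narrower readings are possible. GROC has 15 ranks and is reported by category, so a multinomial model with arm as predictor would be the regression counterpart of its χ² table. Or the sentence may be a loose description of the imputation step, with ANOVA to follow. Neither restriction is stated. The second would still be unsuitable for continuous scores, and pooled estimates belong to the analysis after imputation. What stands is that the primary quantity is stated elsewhere and has not been replaced; the fault lies in the route given for the imputed data.

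An unseen analysis plan could supply detail, but to repair this it would have to contradict a method that the article names. That reply has more force on which analysis decides, since setting complete-case beside imputed results is an ordinary sensitivity comparison. That part is therefore a clarification attached to the main point.

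Four stronger inferences are tempting and not supported:

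- **That FAAM will be categorised, with a calculable loss of power.** Nothing in the article categorises FAAM, and a split into two groups would not be multinomial anyway.
- **That a quarter of FAAM scores are expected to be missing**, from (56 − 42) / 56 = 25%. The inflation also covers participants who cross into or leave treatment. Crossovers are kept as assigned, and leaving treatment does not by itself mean a missing score. The missing-data share is not stated.
- **That there are two primary P values, or that complete-case analysis is itself called intention-to-treat.** The text says neither.
- **That intention-to-treat is absent.** Analysis by assigned group is stated for crossovers.

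**Conclusion.** The point holds as a stated method that is wrong for the primary outcome. Taken at its word, the imputed-data analysis yields log odds ratios and does not estimate the 6-month FAAM difference; the same applies to NPRS and EQ-5D. The complete-case ANOVA would still give a difference in points, so the trial keeps an estimate, but not from the analysis meant to deal with missing scores. The lack of a deciding analysis is a secondary gap.

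No numerical size can be attached. The documents give neither a missing-data rate nor any categorisation of FAAM. The conclusion rests on reading the pooling sentence as covering the outcomes listed for ANOVA, which its unrestricted wording permits. If it was meant for GROC alone, the fault is an unstated scope, and the plan then names no pooling model for FAAM.

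**What to change.** Delete the multinomial sentence for continuous outcomes, or restrict it expressly to a categorical outcome such as GROC. Suggested replacement:

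> In each imputed data set, a linear or mixed model corresponding to the planned FAAM comparison is fitted. The between-group mean difference at 6 months and its standard error are pooled by Rubin's rules and reported with a 95% confidence interval. NPRS and EQ-5D are handled in the same way. The analysis of participants as randomised using the imputed data is primary; the complete-case analysis is a sensitivity analysis.

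Add a clause saying how the primary analysis set relates to the post-randomisation exclusions that the blinded adjudication committee may make, so that the two statements agree.

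The repair does not require a different primary model. Baseline adjustment, for example, is a separate choice. The cost is a change of wording and a standard pooling step, with no effect on sample size, visits or data collection.

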The number of participants for this study is based on the power needed to detect between-group differences in the primary outcome measure, the FAAM, at 6 months. In the absence of research comparing physical therapy and podiatry interventions or podiatry interventions using the FAAM as an outcome measure, sample size calculations are based on achieving a clinically meaningful difference between the groups and details from a recent clinical trial by Cleland et al. [10] that used similar methods to this investigation. Sample size estimate was made using G*Power 3.1.5 based on detecting a difference between groups greater than the minimal clinically important difference (MCID) (i.e., 9 point change) of the FAAM at 6 months with an alpha level of 0.05, 80% power, and pooled sample variance of 14.5 from Cleland et al. [10,30,32]. This resulted in an effect size of 0.62 and 42 participants needed per group. To account for participants who drop-in or drop-out of treatment, in addition to the possibility of some participants not returning the FAAM questionnaire, the sample will be increased by 33% resulting in 56 participants per group. The focus, and consequently the power analysis of this investigation is on functional outcome (based on FAAM scores) and therefore may result in underpowered analysis of secondary variables.

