### Intervention

All patients will attend one visit with a podiatrist where the podiatrist will perform an evaluation and provide intervention based upon usual practice patterns. After this visit, the patient will be invited to participate in the study and undergo a baseline examination that will collect data on variables indicated by Table 1. A member of the office staff will randomize group assignment using random block sizes of 4 and 6, and concealed envelopes containing group assignment to ePT or uPOD (Figure 1).

**Table 1 T1:** Baseline measures of participant characteristics

**Characteristic**	**ePT**	**uPOD**
Age (years)		
Sex		
Height (cm)		
Weight (kg)		
BMI (kg/m^2^)		
Bilateral symptoms (%)		
Prior history of PHP (yes/no)		
Duration of symptoms (days)		
Foot Posture Index [38]		
Number of hours on feet/week		
NPRS		
FAAM		
EQ-5D™		
Healthcare resource use (US dollars)*		
General recovery expectation^†^		
Expectation for physical therapy^‡^		
Expectation for podiatry^‡^		
Treatment Preference (%):		
Neutral		
Physical Therapy		
Podiatry		

*Data derived from a participant-reported questionnaire. ^†^Measured by rating expected recovery according to the GROC scale [34]. ^‡^As measured on a 0–10 visual analog scale where 0 = not helpful and 10 = extremely helpful relative to plantar heel pain. BMI: Body mass index; ePT: Early physical therapy intervention; EQ-5D™: European Quality of Life-Five Dimensions; FAAM: Foot and Ankle Ability Measure; NPRS: Numeric pain rating scale; PHP: Plantar heel pain; uPOD: Usual podiatric care.

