#### Early physical therapy intervention group (ePT)

Individuals in the ePT will be managed by a physical therapist in accordance with the APTA plantar heel pain practice guidelines and recent evidence in support of manual therapy intervention [10,19,25,26]. Treatment provided will be based on identified impairments and may include manual therapy (joint and soft tissue mobilization/thrust manipulation to the lower half of the body), lower leg and plantar foot specific stretching/self-mobilization, foot and lower leg muscle performance training, night splints, taping, over-the-counter orthotics/heel cup/heel cushion, and iontophoresis. The specific intervention will be selected at the discretion of the treating physical therapist, yet will be guided by a manual of procedures that directs intervention priorities and progression based on current best evidence (Tables 2 and 3). The principle investigator will conduct training sessions with each ePT provider to assure comprehension of the items and interventions included in the manual of procedures. Training sessions are estimated to last 1–4 hours per provider and will be conducted in brief sessions with follow-up until each therapist reports comprehension. Participants in the ePT group will be managed by the physical therapist without additional podiatric intervention until the participant achieves a GROC of “quite a bit better” and demonstrates independence in condition management strategies or a plateau in progress demonstrated by GROC or FAAM scores. While participants in the ePT group will be managed primarily by the physical therapist, they are free to return to the podiatrist if they choose.

**Table 2 T2:** Physical therapist guide for intervention delivered to the early physical therapy intervention group

**Intervention category**	**Initial tier interventions**	**Second tier interventions**
Exercise	Stretching/mobility: Plantar fascia-specific, ankle dorsiflexion (knee bent and straight), self-lateral heel glide [10,19]	Stretching/mobility of the posterior thigh [39-41], and identified impairments of areas proximal to the lower leg
		Muscle performance training of foot and lower leg [12,42-47], in addition to identified impairments of proximal regions [48,49]
Manual therapy	Impairment based treatment directed at the ankle and foot [10,25,26]	Impairment based treatment directed at regions proximal to the ankle and foot including neurodynamic impairments [10,50,51]

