#### Usual podiatric care group (uPOD)

Individuals in the uPOD group will receive care typical of podiatric management of PHP at the Des Moines University Clinic that is in accordance with the recently updated practice guideline [20]. According to the guideline [20], the first 6 weeks of treatment includes foot taping/padding, home stretching exercises, over-the-counter arch support/heel cup, shoe recommendations, oral anti-inflammatories, and corticosteroid injections. If the participant is non-responsive to the first 6 weeks of treatment, the guideline indicates the next 6 months of treatment should include corticosteroid injections, custom orthotics, a night splint, immobilization, and referral to a physical therapist [20]. If the participant is not responsive after 6 months of treatment, extracorporeal shock wave therapy or a fasciotomy surgery is recommended per the guideline [20]. Extracorporeal shock wave therapy is not available at Des Moines University and partial or full fasciotomy is performed in less than 1% of patients. In addition to the treatment indicated above, the podiatrist may order radiographs or ultrasound imaging within their scope of practice. The specific intervention will be selected at the discretion of the treating podiatrist and Figure 2 indicates the prevalence of intervention and testing procedures from a random sample of care episodes between February 2008 and August 2011 at the Des Moines University Podiatry Clinic.

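### The analysis is called intention-to-treat, yet randomised participants who received no intervention (undefined) may be excluded, which can bias the 6-month FAAM comparison

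*Protocol article*

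**What the plan says.** Four statements in the protocol article bear on this point.

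- **Label.** Statistical analysis: "Intention-to-treat analysis will be performed by comparing the complete case analysis to multiple imputation analysis".
- **Exclusion rule.** The same paragraph covers randomised participants who proved ineligible or "that did not receive intervention will be considered for exclusion of the analysis by an independent, blinded adjudication committee". The committee is to look at every randomised participant. Receipt of intervention is not defined.
- **Crossovers.** The paragraph continues: "Any crossovers will be analyzed in the original group to which they were assigned". A separate analysis without crossovers is added. No equivalent separate status is given to exclusion for non-receipt, and no analysis without those exclusions is stated.
- **Order of care.** Intervention section: "All patients will attend one visit with a podiatrist where the podiatrist will perform an evaluation and provide intervention based upon usual practice patterns". Only then does recruitment start: "After this visit, the patient will be invited to participate in the study and undergo a baseline examination". Randomisation follows. After it, "Individuals in the ePT will be managed by a physical therapist in accordance with the APTA plantar heel pain practice guidelines", whereas "Individuals in the uPOD group will receive care typical of podiatric management of PHP at the Des Moines University Clinic". No minimum number of further podiatry visits is set.

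**The concern.** Whether a participant goes on to receive care is settled after randomisation and can depend on the arm, on early recovery or on disengagement. Removing people on that ground compares groups that randomisation no longer balances, and it contradicts the intention-to-treat label.

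The design also makes unequal removal plausible. At allocation, a participant in usual podiatric care (uPOD) has already had a treatment visit of the kind their arm provides. An ePT participant has not, and must still make a first contact with a different provider. What is at stake is the primary comparison: FAAM at 6 months, planned around a 9-point difference.

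**Working it through.** **1. The plan's own figure.** Inputs from the Participants section: a 9-point difference, "with an alpha level of 0.05, 80% power, and pooled sample variance of 14.5". The value 14.5 must be a standard deviation, because 9/14.5 = 0.62 is the stated effect size. Taking the test as two-sided (the sample-size text does not say), the noncentral t calculation gives power 0.793 at 41 per group and 0.803 at 42, so the stated 42 reproduces. Inflation: 42 × 1.33 = 55.9, hence 56 per group. The sample size is not in dispute. It supplies the SD and n used below.

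**2. Whom the rule can reach.** The undefined term has three possible readings.

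| Reading of intervention received | uPOD participant who never returns | ePT participant who never attends physical therapy |
|---|---|---|
| Care of the assigned type, with the visit before randomisation counting for uPOD | kept | removable |
| Assigned care after randomisation | removable | removable |
| Any care at all | kept | kept |

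The first reading affects ePT only. The second affects both arms, possibly at different rates. The third leaves the rule empty. Under either reading that removes anyone, selection is on post-randomisation behaviour.

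**3. Overlap with the crossover rule.** The ePT section leaves participants free to go back to the podiatrist. One who skips physical therapy and does so could be a crossover, who is kept, or a person who did not receive intervention, who is removable. The text does not say which rule governs.

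**4. Size, as an illustration.** The documents give neither a non-receipt rate nor a prognostic difference, so both are assumptions. Let a share q of one arm be excluded, let those people have a mean D points below the rest, let the other arm contain the same mix and lose nobody, and let there be no true effect. The full-arm mean is then the mean of those retained minus qD, so:

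- bias = q × D
- SE = 14.5 × √(1/[56(1 − q)] + 1/56)
- type I error = Φ(bias/SE − 1.96) + Φ(−bias/SE − 1.96)

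| q | D | Bias (points) | SE | Type I error |
|---|---|---|---|---|
| 5% | 9 | 0.45 | 2.78 | 5.3% |
| 10% | 9 | 0.90 | 2.82 | 6.2% |
| 20% | 9 | 1.80 | 2.91 | 9.5% |
| any | 0 | 0 | – | 5% |

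With 42 analysed per group and D = 10, SE = 14.5 × √(2/42) = 3.16. Then q = 10% gives a bias of 1.0 and an error of 6.2%, and q = 20% gives 2.0 and 9.7%. Against the 9-point target, 0.45 to 2.0 points is 5% to 22%.

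The sign of D is unknown. Disengaged non-starters might score lower and those who recovered early higher, and a mixture would partly cancel. If both arms lose people, the bias is q₁D₁ − q₂D₂, which is zero only if the two products match.

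**The case against.** The strongest defence is that the rule is narrow. Exclusion is considered case by case and is not automatic. An independent, blinded committee decides, and its procedure rests on a cited reference that is not at hand. Crossovers are kept. People unwilling to comply with either treatment are excluded at entry, so non-starters may be few. Most of this stands, and it limits the likely size. It does not remove the problem: discretion and blinding guard against partial judgement, but a person dropped for not attending is still selected by attendance.

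A reader might infer two stronger points that the documents do not support.

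- **That the rule can remove people from ePT only.** This holds only if the visit before randomisation counts as uPOD intervention. That visit precedes consent and is common to both arms, and uPOD is described as continuing care, so a uPOD participant who never returns could also qualify.
- **That the committee cannot be blind.** A file recording only that no visit took place after allocation, without naming the provider, need not reveal the arm. Blinding may be hard to keep if the fact judged is attendance at physical therapy, but the text does not show that it must fail.

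Nor can the article's brevity explain the rule away. This is a stated rule, not a detail left to the full protocol or the analysis plan.

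**Conclusion.** The concern holds in this form: the exclusion ground conflicts with the intention-to-treat label, is undefined, overlaps with the crossover rule, and can bias the primary comparison. Unequal impact, probably greater in ePT, is plausible from the order of care but not established.

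The illustrated bias of about 0.5–2 FAAM points, with type I error of about 5.3–9.7%, rests on four assumptions: 5–20% of one arm excluded, every such person actually removed, none removed from the other arm, and a uniform 9–10 point difference in prognosis. It is not an estimate for this trial. Bias is zero if those removed have the same prognosis as those kept, and its direction cannot be known in advance. The point should be settled before analysis because the flaw is in the rule itself and is easily removed.

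**What to change.** In the Statistical analysis section:

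1. Remove non-receipt of intervention as a ground for exclusion from the primary analysis.
2. State that the primary analysis includes every randomised participant in the assigned arm, with missing outcomes handled by the multiple imputation already planned.
3. Limit any post-randomisation exclusion to ineligibility shown by information recorded before randomisation, judged blind to arm and outcome.
4. If an analysis without non-receivers is wanted, define receipt of intervention for each arm, say how it relates to crossover, and report it as a sensitivity analysis beside the planned one excluding crossovers.

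The cost is a few lines of text, with no extra participants or data. The increase from 42 to 56 per group already allows for participants who drop in or out of treatment and for unreturned questionnaires.

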Participant expectations and preferences for ePT or uPOD will be categorized into three categories; matched, unmatched, and neutral. Participants will be labelled ‘matched’ if they are allocated to a group for which they have expressed a higher expectation of benefit. A higher expectation will be denoted by comparison of visual analog ratings between the groups (ePT and uPOD; Additional file 1). Unmatched participants will be those who are allocated to the treatment group for which they have a lower expectation of benefit. Neutral participants will be those who indicate the same level of expectation for both treatments. Similar categorizations will be made for participant preference based upon their response to the treatment preference question (Additional file 1). General expectations of improvement will be dichotomized into met or unmet based upon rankings at the 6-week, 6-month, and 1-year follow-up relative to baseline rankings. Participants that demonstrate 6-week, 6-month, and 1-year ranks equal to or higher than baseline will be considered to have met their global expectations of improvement. Participants that demonstrate rankings below baseline expectations will be considered to have unmet global expectations of improvement. A χ^2^ test of independence will be used to compare the proportions of individuals with matched/unmatched/neutral expectations or preferences to global expectations (met or unmet). In addition, differences in expectation and preference categories will be analyzed relative to treatment success using a χ^2^ test of independence. Treatment success will be determined by the GROC at each period with success defined as a GROC of +5, “a great deal better”, or greater.

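### Treatment-specific expectation is analysed only by which of two 0–10 ratings is larger, so the level of benefit expected from the allocated treatment never enters the analysis of GROC success

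*Protocol article*

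**What the plan says.** The Abstract (Methods) announces an analysis of "The association between successful outcomes based on GROC score and participant expectations of recovery generally, and specific to physical therapy and podiatry treatment".

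Table 1 (Methods, Intervention) lists two separate baseline items, expectation for physical therapy and expectation for podiatry. Each is scored on a "visual analog scale where 0 = not helpful and 10 = extremely helpful relative to plantar heel pain".

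The second paragraph of Statistical analysis says how these ratings are used: "Participant expectations and preferences for ePT or uPOD will be categorized into three categories; matched, unmatched, and neutral". The rule for the label is "A higher expectation will be denoted by comparison of visual analog ratings between the groups". For ties, "Neutral participants will be those who indicate the same level of expectation for both treatments". The test is that "differences in expectation and preference categories will be analyzed relative to treatment success using a χ^2^ test of independence", with success meaning a GROC of +5 or more at each follow-up.

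The article describes no other analysis of the numeric ratings against GROC success. They also appear as baseline characteristics, and could become covariates in the analysis of covariance if the groups differ on them. Neither use relates expectation to success.

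**The concern.** The label keeps the order of the two ratings and drops their size. Someone who rates physical therapy 10 and podiatry 9 and is allocated to uPOD is unmatched, despite expecting 9 out of 10 from the care received. Someone who rates the two treatments 3 and 2 and is allocated to the one rated 3 is matched, despite expecting little. Ratings of 9 and 9 and of 1 and 1 are both neutral.

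If success depends on how much a participant expects from the treatment they get, the label is an indirect measure of it. A non-significant χ² could then be read as showing that treatment-specific expectation is unrelated to success, which this test does not directly address. The relative question is also partly covered already, because the same paragraph applies the matched, unmatched and neutral scheme to a separate treatment-preference item. What the ratings add is the amount of benefit expected, and the coding removes it.

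**Working it through.** **1. Sample sizes (protocol, Participants).** The protocol gives no power for the expectation analysis, so its primary-outcome sizes are used. Effect size = 9/14.5 = 0.62, with 14.5 entered as an SD. A two-sided two-sample t-test at alpha 0.05 and 80% power gives 41.7, so 42 per group, as stated. 42 × 1.33 = 55.9, so 56 per group, as stated. The totals are 84 evaluable and 112 enrolled.

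**2. Assumptions, none of them in the protocol.** Both ratings have mean 7 and SD 2, limited to 0–10, with correlation ρ between them. Allocation is 1:1 and success is about 50%. Success follows a logistic model under one of two mechanisms:
- Level: logit(success) = ln(OR) × (rating of allocated treatment − 7)/2.
- Gap: logit(success) = ln(OR) × (allocated − other rating)/SD of that difference.

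Under the level mechanism, an odds ratio of 2 per SD is exp(ln 2 / 2) = 1.41 per rating point.

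**3. Label against the relevant number.** The planned 3×2 χ² is compared with a 1-df test on the number that drives success. Ratings are whole points, OR is 2 per SD, and there are 1,500 simulated trials per cell (Monte Carlo standard error at most √(0.25/1500) = 1.3 points). Power in %:

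| ρ | Level, n=84: χ² / rating | Level, n=112: χ² / rating | Gap, n=84: χ² / gap | Gap, n=112: χ² / gap |
|---|---|---|---|---|
| 0 | 30.9 / 83.1 | 40.9 / 90.5 | 60.3 / 83.5 | 72.5 / 91.5 |
| 0.3 | 23.5 / 81.1 | 30.9 / 91.1 | 59.1 / 79.7 | 74.5 / 90.9 |
| 0.5 | 19.3 / 80.6 | 24.5 / 90.7 | 62.8 / 84.7 | 74.6 / 92.3 |
| 0.7 | 13.7 / 82.1 | 15.2 / 92.0 | 64.2 / 85.1 | 76.1 / 92.1 |
| 0.9 | 9.5 / 81.9 | 10.8 / 91.3 | 76.8 / 89.4 | 88.7 / 95.9 |

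**4. Label against a model that need not know the mechanism.** The comparator is now a logistic model with arm and both ratings, testing the two ratings jointly (2 df). OR is 2 per SD and ρ runs from −0.3 to 0.7.
- Level mechanism: χ² has roughly 13–37% (n=84) and 15–51% (n=112).
- Gap mechanism: χ² has 54–62% and 67–72%.
- The two-rating model has about 71–75% and 83–86% under either mechanism.

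Separate runs put the low end of χ² under the level mechanism at n=112 at 12%, 15% and 16%. Adding participants should not lower power below the 13% seen at n=84, so I treat 12% as simulation noise and use 15%.

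**5. Smaller effect.** At OR 1.5 under the level mechanism, χ² has 5–14% (n=84) and 6–16% (n=112) for ρ from 0 to 0.9. The single rating has only 39–43% and 50–52%. The two-rating model spends a further degree of freedom, so it is underpowered too.

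**6. How often label and level disagree.** With ρ = 0.5 and half-point ratings, about 35% of unmatched participants would rate their allocated treatment 7 or more, and about 27% of matched participants would rate theirs below 7.

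**The case against.** The protocol openly defines a relative question: was the participant allocated to the treatment with the higher expectation, the lower, or neither? The label expresses that directly, and the 10-and-9 and 3-and-2 cases are classified as intended. The abstract sentence names no scale or level and can be read as a summary of this scheme. This stands. It means that the matched/unmatched test is a legitimate analysis and need not be reduced to a description.

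A reader might infer that the planned test has little chance of finding an association, or will usually miss it. The documents do not support that without condition, because they give no rating distribution, correlation, success rate or effect size. If matching itself drives success, χ² does reasonably well. For success of 65% against 35% with 20% neutral, there are 84 × 0.8/2 = 33.6 or 112 × 0.8/2 = 44.8 participants per category, and the matched-versus-unmatched comparison has 70% or 82% power. Power against a level effect also rises as the correlation falls, and the ratings could be negatively correlated if people favour one discipline. The simulated success model is linear in the ratings, which favours the regression.

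The stakes are modest. The expectation analysis belongs to none of the three aims, and the Participants section concedes that analyses of secondary variables may be underpowered. That concession attributes low power to sizing the trial on the FAAM. It does not cover power lost through coding, which the same participants and data could recover. Nor does anything in the article say that a null χ² would be reported as no relation; that is a risk of interpretation only.

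**Conclusion.** It holds as a cheap improvement to a secondary analysis. That the level expected of the allocated treatment is never related to GROC success can be read from the text and needs no assumption. The power cost is conditional on the inputs in step 2 of the working. At an odds ratio of 2 per SD it is large if success follows the level. If success follows only the gap, it is about 10 to 20 percentage points against the two-rating model (for example 54–62% against 71–75% at n=84). In the settings simulated, with correlations from −0.3 to 0.7, the two-rating model did better under both mechanisms. At an odds ratio of 1.5 recoding helps but does not cure the shortage of participants. No treatment comparison depends on this point.

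**What to change.** In Statistical analysis, add as the main analysis of treatment-specific expectation a logistic regression of GROC success (+5 or more) at each visit. Its terms are allocated arm, the baseline rating of the allocated treatment and the baseline rating of the other treatment, with both ratings kept continuous. Report the odds ratio per point with its 95% confidence interval for each rating, and the joint 2-df test of the two.

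Retain the matched/unmatched/neutral χ² as a supporting analysis of matching. State that a non-significant χ² will not be read as showing that expectation is unrelated to success.

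The cost is a change of wording, one or two degrees of freedom, and an assumption that the log-odds are linear in the ratings. Both ratings are already collected, so no new data or participants are needed.
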